### Exploratory outcomes

Anticipated exploratory outcomes are to:

Validate AiDA as a better non-invasive method to establish degree of emphysema in diagnosis of COPD.Validate regenerative processes, matrix turnover, stem/progenitor cell activity in the in vitro models that recapitulate the microenvironment of distal lung tissue from COPD subjects using DLS and PCLS in our developed physiomimetic stretch system [13] and assess how these processes are modulated by exercise.Identify key signaling pathways involved in extracellular matrix turnover, stem/progenitor cell activity, and inflammatory regulation within the in vitro COPD model, and determine how these pathways interact synergistically with mechanosensing signaling cascades activated by exercise-mimicking mechanical stimuli.

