### Specific aims

Study the effects of physical exercise on lung function parameters linked to structural properties e.g., elasticity, stiffness and distal air space dimensions.Validate IOS and AiDA as sensitive and non-invasive tools for detecting changes in lung physiology, and determine their correlation with CT-derived emphysema measures.Evaluate the effect of physical exercise intervention on lung physiology as measured by IOS and AiDA, and assess how these changes relate to changes in symptom burden and quality of life.Evaluate changes in biomarkers before and after the exercise intervention related to regenerative processes, extracellular matrix turnover, stem/progenitor cell activity, and inflammatory patterns in lung tissue biopsies, blood- and urine samples. Correlate these changes with: (a) pulmonary function testing indices, (b) physical capacity, (c) health-related quality of life.Explore the association between structural lung changes, as characterized by high-resolution computed tomography imaging (HRCT), and systemic biological responses, as measured by circulating and urinary biomarkers.Investigate cellular behavior and tissue remodeling/regenerative responses in vitro using models derived from COPD subjects and evaluate how these processes are modulated by exercise-induced systemic changes.

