### Trial design

This trial, “Tissue Regeneration and Exercise” (T-REX), is designed as a multi-center exploratory, hypothesis-generating single group trial exploring the mechanisms for lung regeneration in people with COPD induced by a 12-week exercise intervention. The project is divided into four parts; [1] basic baseline survey and testing; [2] a 12-week exercise intervention; [3] analysis phase; and [4] in vitro characterization. Figure 1 gives an overview of the study design.

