### Eligibility criteria

#### Inclusion criteria

Participants will be adults with a diagnosis of COPD. To be eligible for participation in the study, participants must have:

Forced expiratory volume in one second (FEV_1_)/Forced vital capacity (FVC) < 0.7.Postbronchodilator FEV_1_ of 30–85% of predicted value.Optimal medical treatment according to GOLD and the Swedish National Guidelines.Former smokers, ≥ 10 pack-years, smoking history, but had to be an ex-smoker for ≥ 1 year.Free from exacerbations in the last 6 weeks.Age: 50–85 years.BMI: 18–37 kg/m^2^.

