### High resolution computer tomography (HRCT)

High resolution computer tomography (HRCT) will be performed according to clinical routine. Emphysema will be classified as centrilobular, panlobular or paraseptal. Additional visual features to be evaluated include airway wall thickening, small airway disease, tracheal and interstitial abnormalities, pulmonary arterial enlargement and bronchiectasis [38]. Grading of emphysema will be done as volume with low and high attenuation density of the respective lung. A Specialist in Clinical physiology will quantify volumes with low and high attenuation density in the lung tissue from the HRCT pictures, by means of an objective imaging density measurement.

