## Discussion

In this study, we aim to identify mechanisms that activate regeneration of lost lung tissue to restore lung function in COPD, i.e. stimulating health- and not disease factors. Our hypothesis is that adjusted exercise training improves disease outcomes in subjects with COPD by inducing inherent regenerative processes or block further remodeling in the lung. By gaining deeper insight into the molecular and cellular responses triggered by exercise training, we aim to identify the key repair pathways involved, thus paving the way for potential enhancement through targeted pharmacological interventions. Furthermore, we expect to identify biomarkers mirroring these processes systemically to enhance our ability to monitor disease activity, personalize therapy, and stratify subjects into responders and non-responders. Moreover, we aim to validate IOS and AiDA as sensitive, non-invasive tools for detecting early physiological changes and disease progression, potentially more accurately than conventional spirometry, particularly for assessing small airway and distal lung pathology. We foresee that this project may create a foundation for other patient groups, where an early intervention with adjusted exercise training may have a substantial impact on recovery time and quality of life.

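### The single-group, all-COPD sample cannot show that AiDA helps diagnose COPD, and AiDA's correlation with CT alone cannot show that it is better than another test

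*Protocol article*

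**What the plan says.** Under Exploratory outcomes, the protocol article plans to "Validate AiDA as a better non-invasive method to establish degree of emphysema in diagnosis of COPD". The sentence names no comparator.

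Under Inclusion criteria, "Participants will be adults with a diagnosis of COPD", with "Forced expiratory volume in one second (FEV_1_)/Forced vital capacity (FVC) < 0.7" and "Postbronchodilator FEV_1_ of 30–85% of predicted value". Trial design describes a "multi-center exploratory, hypothesis-generating single group trial". Healthy material is mentioned only as lung tissue for the in vitro platform (Background).

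For validation against a reference, Specific aims says of IOS and AiDA that the study will "determine their correlation with CT-derived emphysema measures". The HRCT section supplies a graded reference: "Grading of emphysema will be done as volume with low and high attenuation density of the respective lung".

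The Discussion describes IOS and AiDA as "sensitive, non-invasive tools for detecting early physiological changes and disease progression, potentially more accurately than conventional spirometry". Assessments are at baseline, 6 weeks and 12 weeks, and all participants exercise.

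**The concern.** Three claims go further than the stated design.

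- **Diagnosis.** Accuracy for diagnosing COPD needs people with and without COPD. Here everyone has it.
- **Better.** Superiority needs a second test set against the same reference in the same people, with the difference estimated. A correlation of AiDA with CT describes AiDA alone.
- **Disease progression.** Progression is worsening over the natural course. A short period in which everyone receives an intervention expected to help, with no concurrent untreated group, does not identify it.

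At stake is how the results may be read. A respectable AiDA–CT correlation could be presented as diagnostic validation. A significant result for AiDA beside a non-significant one for another test could be presented as superiority. The Sample size section adds to that risk, because it treats non-significance at about 80 participants as a sign of limited clinical relevance.

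**Working it through.** **Plan's own figure.** The article plans 80 participants with 10–20% drop-out and gives no correlation, accuracy or power, so 80 cannot be re-derived. The drop-out arithmetic gives 80 × 0.90 = 72 and 80 × 0.80 = 64 completers. A baseline AiDA–CT correlation could use up to 80, less any AiDA measurements rejected for quality. I use 64 to 80.

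**1. Diagnosis of COPD.** Specificity = true negatives ÷ participants without COPD. The denominator is 0, so specificity, ROC area and predictive values are undefined at any sample size.

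**2. Degree of emphysema within COPD.** This is estimable. All correlations below are my assumptions; the documents give none. The 95% CI is tanh(atanh r ± 1.96/√(n−3)).

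| Assumed r | n = 64 | n = 72 | n = 80 |
|---|---|---|---|
| 0.3 | 0.06–0.51 | 0.07–0.50 | 0.09–0.49 |
| 0.5 | 0.29–0.66 | 0.30–0.66 | 0.31–0.65 |
| 0.7 | 0.55–0.81 | 0.56–0.80 | 0.57–0.80 |

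Example: r = 0.5, n = 64 gives 0.549 ± 1.96/√61 = 0.549 ± 0.251, which transforms back to 0.29 and 0.66.

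The smallest correlation detectable with 80% power (two-sided 0.05) is tanh((1.960 + 0.842)/√(n−3)), which is 0.344, 0.325 and 0.309 for n = 64, 72 and 80.

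The intervals for r = 0.3 and r = 0.5 overlap widely. One test reaching significance and another missing it would therefore say little about which is better.

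**3. Better than a comparator.** Let r1 and r2 be the two tests' correlations with CT, k the correlation between the tests, and m = (r1 + r2)/2. The Steiger-type statistic is

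Z = (atanh r1 − atanh r2)·√(n−3) / √(2 − 2c), with c = [k(1 − 2m²) − ½m²(1 − 2m² − k²)] / (1 − m²)².

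For r1 = 0.6, r2 = 0.4, k = 0.4:

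- m² = 0.25, so c = (0.200 − 0.0425)/0.5625 = 0.28 and √(2 − 0.56) = 1.20.
- The difference in atanh is 0.693 − 0.424 = 0.2695.
- n = 64: expected Z = 0.2695 × 7.810/1.20 = 1.75, power ≈ Φ(1.75 − 1.96) = 0.42.
- n = 80: expected Z = 0.2695 × 8.775/1.20 = 1.97, power ≈ Φ(0.01) = 0.50.

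Simulation of the same test (4,000 runs per cell, k = 0.4) agrees:

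| Correlations with CT | n = 64 | n = 72 | n = 80 |
|---|---|---|---|
| 0.7 v 0.4 | 0.82 | 0.87 | 0.90 |
| 0.6 v 0.4 | 0.41 | 0.48 | 0.50 |
| 0.6 v 0.5 | 0.15 | 0.16 | 0.18 |

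**4. Progression.** The Discussion's claim stands beside one arm, three assessment times within a nominal 12 weeks, and exercise for everyone. Change can be measured. It cannot be separated into progression and the effect of training.

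**The case against.** The strongest reply is that the stated target is the degree of emphysema. That is a grading question, it needs no participants without COPD, and HRCT density gives it a reference. This stands. A reader might infer that the AiDA outcome cannot be tested at all; the documents do not support that, because both the grading question and a paired comparison of tests can be answered within COPD.

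A reader might also infer that AiDA is to be validated for early disease, so that an at-risk group is missing. The article does not say so. The Abstract and Discussion speak of early physiological or structural changes, and short-term change can be observed in established COPD.

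It is also fair to say that the article plans other uses of AiDA: its change with exercise, its relation to symptoms and quality of life, and responder classification. The Discussion names spirometry as a comparator and hedges with *potentially*, and the method for comparing tests may sit in an analysis plan that is not shown. I therefore do not count the missing method as a fault. But none of those other uses tests superiority in grading emphysema, and the outcome as worded claims it without saying over what.

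Finally, the outcome is exploratory, which limits the harm to over-interpretation. Nothing in the article shows that the results will in fact be over-claimed.

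**Conclusion.** The point holds in a limited form. Diagnostic accuracy for COPD cannot be estimated, since there are no participants without COPD. The association of AiDA with HRCT emphysema grade can be estimated, within the admitted range of FEV1 30–85% predicted. AiDA's correlation with CT does not by itself support *better*. A paired comparison could, but under the assumed correlations it has good power only for a large gap: 0.82–0.90 for 0.7 v 0.4, 0.41–0.50 for 0.6 v 0.4, and 0.15–0.18 for 0.6 v 0.5. Disease progression is not identifiable from this design.

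The first and last conclusions rest on the design alone. The power figures rest on assumed correlations and approximate normality. The correction is worth making because it changes what the trial may conclude about AiDA; it does not affect the primary outcome.

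**What to change.** - **Exploratory outcomes.** Delete the closing words about diagnosis of COPD. Restate the outcome as the association of rAiDA and R0 with HRCT low-attenuation volume within COPD, compared in the same participants with named tests already measured: at least spirometry, which the Discussion names, and DLCO, IOS and RV/TLC.
- **Basis for *better*.** Use the difference between dependent correlations with a 95% confidence interval, for example by bootstrap, and not separate significance tests. State that participants were selected on FEV1 and FEV1/FVC. This restricts the range of spirometry directly and could weaken its correlation with CT relative to AiDA's.
- **Discussion claim.** Drop *disease progression*, and limit *early* to short-term change within established COPD.

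The cost is narrower claims and one short analysis; no new measurements are needed. Unless the gap between tests is large, the comparison may well be inconclusive, and the report should say so. The article gives the trial as still recruiting, and its Data monitoring section already provides for reporting significant changes to aims or analysis to the ethics committee and the registry, so this can be settled before analysis. A diagnostic claim would need a separate group without COPD.

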### Screening tools

Screening for problematic alcohol use will be conducted using the Cut-down, Annoyed, Guilty, and Eye-opener (CAGE) questionnaire [18] to identify participants at risk of dropout and to support completion of the training period. The questionnaire consists of seven questions, which can be answered with “Yes” or “No.” Two “Yes” responses to questions 2–7 suggest alcohol dependence.

Screening for adequate activity levels will assess participants’ physical activity over a typical week using a questionnaire [19, 20]. Structured exercise (Question 1) will cover activity type, duration, and intensity, while everyday activities (Question 2) will include daily routines, walking habits, and weekly activity patterns. Data from these questions will be used to calculate total activity minutes (exercise minutes ×2 + everyday activity minutes ×1). Participants engaging in organized and regular exercise ≥ 2 times per week will be excluded.

Subjects will be interviewed about medical history, medications, smoking status, exacerbation history and infection status.

### Study procedures

At first visit, all subjects will initially go through a clinical examination including electrocardiogram. Before first measurement the subjects will inhale 400 µg short acting beta-2 agonist (salbutamol, Buventol^®^ Easyhaler) using a valve spacer device. All testing will be performed at least 15 min thereafter in the following order: fractional exhaled NO (FeNO), 6MWT, IOS, Spirometry, Body plethysmography, DLCO, SBW, 1-minute sit-to-stand test, 6MWT no 2 (at baseline visit), Cardiopulmonary exercise testing (CPET) - which might be done at a separate visit. Subjects will be asked to rest when needed between tests, and specifically at least 10–15 min after 6MWT and sit-to-stand test. If the subject fulfills any of the exclusion criteria, no further testing will be performed.

Blood and urine samples will be taken, and questionnaires will be filled in during resting times. Aida will be done on a separate visit.

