### Study outcomes

The primary outcome is to validate the effect in protein profiles after exercise intervention in lung tissue biopsies, blood- and urine samples using proteomic analyses such as multi-plex ELISA, OLINK, and mass spectrometry. Primary factors include; matrix turnover/remodelling proteins: MMPs, TIMPs, MMP-degraded collagen peptides, desmosine, periostin, decorin; growthfactors: VEGF, HGF, PDGF, FGF-2, angiopoietin; inflammatory/immune markers: TNF-a IL-6, IL1-b, IL-8, IL-10, IL-17, MCP-1, CXCL10, CXCl13.

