### Blood samples

All blood samples are collected before 13.00 o’clock to avoid any effect of diurnal variation. Blood will be drawn in EDTA tubes for differential cell count (performed at the hospital routine laboratory), for plasma (collecting the supernatant after 10 min centrifugation in 2000 x g) and for buffy coat (collecting the white blood cell layer after the centrifugation). In addition, serum will be sampled (after 30 min incubation to enable coagulation and collecting the supernatant after 10 min centrifugation in 2000 x g). Samples will be frozen in −80 °C until further analyses. Levels of hemoglobin and alpha-1 antitrypsin will be measured according to clinical routine.

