### Participant timeline

Participants will first be contacted by phone or mail for an initial screening. Before the intervention begins, they will undergo a comprehensive baseline assessment (one to three visits). Following this, participants will engage in a 12-week supervised exercise intervention, with data collection scheduled at mid-intervention (after 6 weeks, one visit) and post-intervention (after 12 weeks, one to three visits).

The baseline and post-intervention assessments will include medication use and health status, clinical examination by a physician, collection of participant data, questionnaires, physical capacity tests, comprehensive pulmonary function assessments, and sample collection.

The mid-intervention assessment will cover medication use, health status, questionnaires, spirometry, and blood sampling.

Participant recruitment is summarized in a flow diagram (Fig. 2), and the schedule of enrolment, intervention, and assessment are presented in the SPIRIT diagram (Fig. 3).

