### Order of assessments and procedures during study visits

The order of assessments and procedures during each study visit has been standardised to ensure consistency and minimise participant burden. At each visit, procedures will be conducted in the following sequence: Fractional exhaled NO (FeNO), 6MWT, IOS, Spirometry, Body plethysmography, DLCO, SBW, sit-to-stand test, 6MWT no 2 (at baseline visit), Cardiopulmonary exercise testing (CPET), which might be done at a separate visit. Subjects will be asked to rest when needed between tests, and specifically 10–15 min after 6MWT and sit-to-stand test. Blood and urine samples will be taken and questionnaires will be filled in during resting times. Aida will be done at a separate visit.

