### Statistical methods

After the last participant has completed all assessments, additional monitoring and data quality checks will be completed. Analyses will be performed by the investigators supported by a biostatistician when needed. All statistical tests will be conducted as two-sided, with the alpha level set at 0.05. Baseline variables and descriptive statistics with continuous data will be presented with mean ± standard deviation (SD) or median with interquartile range (IQR) as appropriate. Ordinal variables will be presented as median (IQR), and categorical variables will be presented as n (%).

Continuous data with normative values (for example lung function values) will be presented both as absolute values and as % of predicted normal values.

The primary outcome is the change from baseline to post intervention, and analyses will be performed with paired statistical testing. Analyses of both absolute change (delta values) and % change will be performed. Age, sex, pack-years and site are potential confounding factors which might be taken into account as co-variates.

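### The point at which primary-outcome blood and urine are drawn is not fixed relative to the exercise tests, so an unequal acute response at the two visits can be confounded with the training effect

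*Protocol article*

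**What the plan says.** The primary outcome (Study outcomes) is to "validate the effect in protein profiles after exercise intervention in lung tissue biopsies, blood- and urine samples". The listed proteins include inflammatory markers and growth factors. Statistical methods defines the contrast: "The primary outcome is the change from baseline to post intervention, and analyses will be performed with paired statistical testing". Trial design describes a single-group exploratory trial.

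The sampling rule appears twice. Study procedures has "Blood and urine samples will be taken, and questionnaires will be filled in during resting times", and Order of assessments and procedures during study visits has "Blood and urine samples will be taken and questionnaires will be filled in during resting times". Study procedures describes the rests: "Subjects will be asked to rest when needed between tests, and specifically at least 10–15 min after 6MWT and sit-to-stand test".

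Both sections give the same order: FeNO, walk, IOS, spirometry, plethysmography, DLCO, nitrogen wash-out, sit-to-stand, then "6MWT no 2 (at baseline visit" only), then CPET, which may be moved to another visit. Order of assessments says that this sequence is standardised and applies at each visit. Participant timeline gives week 6 a shorter list: "The mid-intervention assessment will cover medication use, health status, questionnaires, spirometry, and blood sampling".

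The only timing control for blood is collection before 13.00, "to avoid any effect of diurnal variation" (Blood samples). Urine samples has no timing rule.

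**The concern.** The trial asks what 12 weeks of training does to protein profiles. That calls for samples taken under the same conditions at both ends. The article instead lets the draw float among rests that mostly follow exertion, although it describes the order of procedures as standardised. It controls other short-term influences on the same markers: clock time for blood, and stable disease because raised inflammatory markers could confound the results (Criteria for discontinuing or modifying interventions). It sets no comparable control for exertion shortly before the draw.

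If a marker responds acutely, two things can follow. A systematic difference between visits in preceding load, or in time since exertion, becomes part of the estimated training change, and no control arm removes it. Even with no average difference, a varying position adds noise to the paired difference and costs power. Because the article states the sampling point twice, this is a stated rule that is badly fixed, not detail left to a fuller protocol.

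**Working it through.** **Step 1: where a draw can fall.** Listed exertions before the draw, from the order in Study procedures and Order of assessments:

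| Draw taken | Baseline | Post-intervention |
|---|---|---|
| Before the first walk (not excluded, not required) | 0 | 0 |
| After the first walk, or among the lung function tests | 1 | 1 |
| After sit-to-stand | 2 | 2 |
| After the second walk | 3 | no such point; at most 2 |

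A same-day CPET adds one more exertion for any draw taken after it. Whether it is on the same day is not fixed at either visit.

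**Step 2: how the load can differ between the two visits.**

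- The participant is sampled in different rows at the two visits, which the rule allows.
- The draw is late at baseline, after the second walk.
- CPET precedes the draw at one visit only.
- The row is the same, but walking distance or repetitions have changed. The secondary outcomes look for changes of this kind.

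One further route is inference only. The first baseline walk also serves as an eligibility check, and testing stops if an exclusion criterion is met. Staff therefore have a reason to wait for its result before sampling at baseline, which does not apply after the intervention.

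**Step 3: what is outside the problem.** Lung biopsies are taken at bronchoscopy, so the sampling rule does not touch them. Week 6 lists no exercise test and no urine, and the primary contrast does not use it. An acute response of equal size at both visits cancels in the paired change; only the difference between visits counts.

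**Step 4: illustration of size.** The article gives no acute response, no SD and no power calculation, so there is no figure to reproduce.

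- Pairs: 80 enrolled with 10–20% drop-out gives 80 × 0.9 = 72 to 80 × 0.8 = 64 (Sample size).
- Test: paired t, two-sided, alpha 0.05 (Statistical methods).
- Assumption: no training effect, and an average acute shift between visits of b SDs of the paired difference.

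The rejection probability is P(T > t*) + P(T < −t*). Here T is noncentral t with n − 1 degrees of freedom and noncentrality b√n, and t* is the 97.5% point of the central t.

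| b | n = 64: b√n | n = 64: rejects | n = 72: b√n | n = 72: rejects |
|---|---|---|---|---|
| 0 | 0 | 5% | 0 | 5% |
| 0.1 | 0.80 | 12% | 0.85 | 13% |
| 0.2 | 1.60 | 35% | 1.70 | 39% |
| 0.3 | 2.40 | 66% | 2.55 | 71% |
| 0.5 | 4.00 | 98% | 4.24 | 99% |

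The shift that is declared significant with 80% probability is 0.356 SD (n = 64) or 0.335 SD (n = 72).

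**Step 5: the same shift as a percentage.** With an assumed within-person CV, the SD of the log change is √(2 ln(1 + CV²)): 0.415 for a CV of 30% and 0.668 for 50%. Multiplying by 0.335–0.356 and exponentiating gives ratios of 1.15–1.16 and 1.25–1.27. These are differences in the whole marker level between visits, not in the acute component alone. They describe the sensitivity of the test under assumed CVs and are not evidence that such a shift occurs.

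**The case against.** The strongest reply is that nothing in the article shows unequal exertion before sampling.

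- **The extra walk comes late.** It follows sit-to-stand, so a draw after the first walk, among the lung function tests or after sit-to-stand has the same listed tests before it at both visits. This stands. A reader might infer that exertion before sampling does differ between baseline and week 12. The text supports only that it can.
- **A pre-exertion draw is possible.** Rests may be taken whenever needed, and all testing starts at least 15 minutes after salbutamol. It is unclear whether that wait counts as resting time. This stands too, but permission is not a rule, and the rests that are named follow exertion.
- **The biology is assumed.** The article does not say that these markers respond to a six-minute walk or a one-minute sit-to-stand, and many listed proteins may not. This stands. A reader might infer that training will falsely appear to reduce inflammation, but neither the size nor the direction of a shift is documented.
- **Any bias of that size would give the same rates.** This is true. The 35–71% illustrates sensitivity and does not forecast the trial's error rate.
- **Diurnal variation is already handled.** The 13.00 limit narrows it. At most, the claim to avoid any effect is worded too strongly, which is minor.
- **Week 6 is not comparable.** A reader might count this against the primary outcome. It bears only on trajectory comparisons.
- **It is late to change.** Enrolment began in 2022 and the first round should finish at the end of 2025. Past sampling positions may not have been recorded. Both limit what a change can repair.

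**Conclusion.** The point holds in a limited form. The sampling position for primary-outcome blood and urine is not fixed relative to the exercise tests. On the stated order it normally falls after at least one exertion at the baseline and post-intervention visits, and the preceding load can differ between them. Because the contrast is paired within a single arm, any resulting visit difference in an acutely responsive marker cannot be separated from the training effect.

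The size is unknown. It rests on the assumptions that some markers respond acutely and that the average response differs between visits. Under an assumed 0.2–0.3 SD shift, the per-marker false-positive rate would be about 35–71% instead of 5%. With no shift from this source it stays at 5%. Given the exploratory aim, the late stage of recruitment and the undocumented acute response, this is a worthwhile, inexpensive improvement rather than a defect that invalidates the primary analysis.

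**What to change.** - **Participants not yet at baseline:** draw blood and urine at one fixed point before the first walk and any other exertion, at every visit where they are collected. Keep the draw in the same order relative to the pre-test salbutamol, and at a similar clock time for each participant where feasible.
- **Participants already sampled at baseline:** take later samples at the baseline position where it is known.
- **All samples from now on:** record the time since last exertion. Without it, no later analysis can adjust.
- **Analysis:** add a sensitivity analysis in position-matched pairs, limited to those whose positions were recorded.
- **Text:** reconcile Order of assessments, which applies one sequence at each visit, with the shorter week-6 list in Participant timeline.

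The cost is minor rescheduling within existing visits and one CRF field, with no extra procedure. The downside is a mix of sampling positions between earlier and later participants. The sensitivity analysis can address that only where positions are known.

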### Exercise tests

#### Six-minute walk test (6MWT)

The six-minute walk test (6MWT), a sub-maximal exercise test, is used to assess aerobic capacity and endurance [24]. In the 6MWT, the subjects are asked to walk, in a 30-meter distance, as far as possible during six minutes. The following parameters will be observed: walking distance, SpO_2_, heart rate, perception of dyspnea and leg fatigue every two minutes during the test [25]. The 6MWT will be performed twice at the baseline visit, and the results from the best performance (= longest distance) is used. The MCID is 30 m [25, 26].

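### Blood and urine sampling for the primary outcome is not fixed relative to the exercise tests, so the single-arm paired protein change may include an acute exercise response

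*Protocol article*

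**What the plan says.** Study procedures gives the timing rule for the fluid samples: "Blood and urine samples will be taken, and questionnaires will be filled in during resting times". The section on the order of assessments repeats it: "Blood and urine samples will be taken and questionnaires will be filled in during resting times". The rests are described as "Subjects will be asked to rest when needed between tests, and specifically at least 10–15 min after 6MWT and sit-to-stand test".

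FeNO comes first in the order and the 6MWT second, followed by oscillometry, spirometry and plethysmography. The list ends with "DLCO, SBW, 1-minute sit-to-stand test, 6MWT no 2 (at baseline visit), Cardiopulmonary exercise testing (CPET) - which might be done at a separate visit". The 6MWT section confirms the extra walk: "The 6MWT will be performed twice at the baseline visit, and the results from the best performance (= longest distance) is used". Only one walk is foreseen at week 12.

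The Blood samples section requires blood to be drawn before 13.00 because of diurnal variation. No timing rule is stated for urine.

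On the endpoint: "The primary outcome is to validate the effect in protein profiles after exercise intervention in lung tissue biopsies, blood- and urine samples". Statistical methods defines the primary contrast as the change from baseline to post intervention, tested with paired methods at two-sided 0.05. Trial design describes a single group.

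For week 6, Participant timeline states: "The mid-intervention assessment will cover medication use, health status, questionnaires, spirometry, and blood sampling". The section on the order of assessments, however, begins: "At each visit, procedures will be conducted in the following sequence: Fractional exhaled NO (FeNO), 6MWT, IOS, Spirometry".

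**The concern.** The samples that carry most of the primary outcome have no position of their own in a visit order that is otherwise standardised. They go into the rests, and the rests that the plan requires come directly after exertion. Clock time is controlled for blood, so the plan accepts that the state at sampling matters. Exertion, the factor closest to the intervention itself, is not controlled.

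The named markers include IL-6, IL-8, TNF-α, VEGF and HGF, and the aim is to read their change as an effect of 12 weeks of training. If such a marker also moves after a single walk or sit-to-stand test, part of the paired difference reflects what the participant did shortly before the draw. With no control group, nothing in the design removes that part. Bronchoscopy is planned for 20 of the 80 participants, so for most of them the primary outcome rests on blood and urine alone. The state at sampling cannot be corrected once the sample is in the freezer.

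**Working it through.** **Exercise that may precede a draw, by visit**

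| Visit | Exercise tests in the plan | Position of the blood/urine draw |
|---|---|---|
| Baseline | 6MWT, sit-to-stand, second 6MWT; CPET same day or separate | any rest; not fixed |
| Week 6 | none in Participant timeline; full sequence under the order of assessments | blood only; not fixed |
| Week 12 | 6MWT, sit-to-stand; CPET same day or separate | any rest; not fixed |

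Three situations are compatible with the text:

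1. Both draws come before the first 6MWT, for example in the wait of at least 15 minutes after the bronchodilator. No test-related response enters.
2. Both draws come after the first 6MWT. The nominal load is equal, but the walk is self-paced and training may change the acute response to it.
3. The draws fall in different rests. The load then differs between visits, most of all if the baseline draw follows the second walk or a same-day CPET.

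The plan does not say which applies, or that the same one applies to a given person at both visits.

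**How large a shift would matter**

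The plan gives no power, effect size or SD with its sample size, so there is no figure of its own to reproduce.

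Inputs from the protocol article: 80 participants, 10–20% drop-out, two-sided alpha 0.05, paired test. If the 80 are counted before drop-out, the pairs number 80 × 0.8 = 64 to 80 × 0.9 = 72.

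Assumed inputs: SD of the within-person log change s = 0.4 to 0.6, no training effect, and a systematic difference d between visits in the acute response.

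Formula: mean shift m = ln(1 + d); noncentrality λ = m√n / s; rejection probability = P(|T| > t₀.₉₇₅,ₙ₋₁), where T is noncentral t with n − 1 degrees of freedom and noncentrality λ.

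- d = 5% in everyone: m = 0.0488. With s = 0.6 and n = 64, λ = 0.0488 × 8 / 0.6 = 0.65, giving 9.8%. With s = 0.4 and n = 72, λ = 1.04, giving 17.5%.
- d = 10% in everyone: m = 0.0953. The same two corners have λ = 1.27 and 2.02, giving 24.0% and 51.4%.
- d = 10% in half the participants, same SDs: m = 0.0477, giving 9.6–16.9%.
- d = 10% in a quarter of them: m = 0.0238, giving about 6–8%.
- d = 0: 5%.

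The same result without a log-change SD: a shift of 0.2 SD of the paired difference gives 35.1% (n = 64) to 38.8% (n = 72). For comparison, the change detectable with 80% power is (1.960 + 0.842)/√n = 0.35 to 0.33 SD. A shift well below what the trial could reliably detect is therefore enough to raise the per-marker error rate several-fold.

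**The case against.** The strongest counter-argument is that the text leaves the rest period open and does not place the draw after exercise. That is correct. A reader might infer that baseline samples are taken under a heavier load than week-12 samples. The documents permit this but do not establish it. The second walk matters only if the baseline draw follows it, late in a sequence whose blood sampling must be finished before 13.00, and assessments may be spread over one to three visits.

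A reader might also infer that the artefact would produce the fall in markers that the investigators hope for. The documents do not support a direction. The hypothesis has two parts, less harmful remodelling and inflammation and more regenerative activity, and gives no direction marker by marker. An apparent fall in VEGF or HGF would tend to count against the second part. Any residue of a recent training session at week 12 would act against an excess at baseline.

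Three limits also stand. Week 6 lies outside the primary contrast and lists no urine, so its lower load cannot bias the primary change. Biopsies come from bronchoscopy and are not governed by this rule. The lack of a stated minimum interval since the last training session is a detail that an article may leave to the full protocol, and it is not counted here as a fault.

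The trial is exploratory, and the article says that testing follows standardised procedures. Neither answers the point. A slot is stated, twice, and as stated it allows sampling after exertion and in different states at the two visits.

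**Conclusion.** The concern holds as an uncontrolled risk of unknown size and direction. As written, the plan lets an acute exercise response enter the paired change in blood and urine proteins, and the single-arm design cannot separate it from the training effect. It does not show that this happens, or that the load before the baseline and week-12 draws is unequal.

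The percentages are illustrations. They rest on an assumed log-change SD of 0.4–0.6, on 64–72 pairs, and on assumed shifts of 5% and 10% that apply to every participant. No acute-response size is given in the documents. If only some participants are affected, the inflation is smaller and may be slight.

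**What to change.** In Study procedures and in the section on the order of assessments, replace the resting-times rule for samples with one fixed slot: blood and urine at seated rest, before the first 6MWT and any other exercise test, identical at every visit where they are collected. Add CRF fields for the tests completed before each draw and the date of the last training session.

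For participants whose baseline sample already exists (enrolment began in 2022), repeat the recorded baseline slot at follow-up. Report the sampling state, and add a sensitivity analysis of the primary outcome restricted to pairs drawn in the same state.

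Reconcile Participant timeline with the order-of-assessments section on whether exercise tests are done at week 6.

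Cost: a reordering within existing visits and two short CRF entries. There are two downsides. Some samples will come from people later excluded for desaturation at the 6MWT, if that screening walk is the baseline one. Sampling states will be mixed among those already enrolled, and the sensitivity analysis can address this only where the slot was recorded or can be reconstructed.
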